#### **4.4 Criteria of Dropout**

Participants included in the study should be classified as dropout (with missing data but not excluded in the analyses) if they meet any of the following criteria:

- ① Lost to follow-up during the study period;
- ② Request to withdraw the informed consent;
- ③ Other circumstances that affect the completion of follow-up visits.

### **Section 5. Sample Size**

The minimal clinically important difference (MCID) of the primary outcome varies among studies, ranging from 8 to 40 for each subscale among patients with knee injuries or osteoarthritis. Based on the anchor-based method, the MCIDs are 10.7–16.7 for the 4 subscales, averaged 13.8. Therefore, the statistical hypothesis is based on detecting a between-group difference of 13 points. The maximum SD is estimated to be 20 points, thus the effect size is 0.65. With the 2-sided significance level and power setting at 0.05 and 0.9, respectively, a sample size of 51 participants is required in each group (1:1 allocation, calculated using G\*Power 3.1, based on the test of mean difference between two independent groups, and assuming a balanced baseline). After adding the dropout (estimated within 15%), a total of 120 participants (60 in each group) should be included in this study.

### **Section 6. Participant Recruitment**

#### **6.1 Inclusion and Exclusion**

Participants who are scheduled to undergo ACLR and hospitalized in the department of sports medicine in our institution will be screened for eligibility. After checking the inclusion and exclusion criteria, the study information will be introduced to eligible patients. For patients who are interested in participating the trial, oral informed consents will be carried out and written informed consents will be signed if they decide to participate. The oral and written informed consents will include detailed protocols of intervention and outcome measures, as well as potential benefits and risks throughout the trial. Patients are informed that the conventional surgical and rehabilitation treatment (following the SOP) as well as follow-up visits will not be affected no matter whether they decide to participate or not.

In particular, the inclusion and exclusion criteria involve demographic characteristics, injury patterns, medical history, and surgical details. Although most criteria can be checked before surgery, cartilage defect and meniscal treatment should be confirmed under arthroscopy during surgery. The exclusion criteria will be rechecked after surgery to exclude patients with severe cartilage defect or meniscal repair (because of distinguished rehabilitation programs and objectives from isolated ACLR or ACLR with meniscal resection).

## **6.2 Baseline Evaluation**

- ① Demographic characteristics (self-reported, before surgery): age, gender, body mass index, affected side, Beighton score (hypermobility), preinjury Tegner score (sports level), types of sports participation at injury, and time from injury to surgery.
- ② Subjective assessments (in written forms, before surgery): Knee Injury and Osteoarthritis Outcome Score (KOOS), P4 score for pain, Lysholm score, and subjective International Knee Documentation Committee (IKDC) score.
- ③ Physical examinations: knee range of motion and knee circumference at the mid-patellar level (before surgery); knee laxity (under anesthesia, during surgery).
- ④ Surgical details: amount of ACL remnant, graft diameters (for anteromedial and posterolateral bundles), and meniscal treatment (none or meniscal resection).

## **6.3 Surgical Procedures**

Participants included in this study will receive conventional anatomic double-bundle ACLR using hamstring autograft following the institutional SOP:

### **① Position and diagnostic arthroscopy**

The patients is in the supine position, with the affected knee flexed at 90°, and a baffle is placed on the outside of the proximal thigh. The arthroscope is inserted from the anterolateral approach to observe the ACL injury and confirm the diagnosis.

### **② Autograft harvest and preparation**

Through the skin and sartorius aponeurosis incisions, the autologous semitendinosus tendon (ST) and gracilis tendon (GT) are recognized, ligated, and torn off the tibial insertions with the periosteum. After cutting the connecting fibers, the ST and GT are harvested using a tendon stripper. The ST and GT are braided and folded into two 4-stranded grafts, which are separately passed through a non-slotted diameter measurement tool.

### **③ Tunnel positioning and creation**

The femoral and tibial footprint centers of the ACL are located and marked using a radiofrequency probe. For each bundle of the ACL, a tunnel positioner is inserted from the anteromedial approaches and positioned at the tibial attachment, and the guide pin is drilled through the positioner towards the femoral attachment. The tibial and femoral tunnels of the anteromedial and posterolateral bundles are sequentially created using the guide pin.

#### ④ Proximal and distal graft fixation

The proximal ends of the 4-stranded ST and 4-stranded GT are separately pulled from the tibial tunnels through the joint cavity to the femoral tunnels. The suture tapes on the proximal graft ends are fixed on cortical buttons over the outer orifices of the femoral tunnels. With the patient at full knee extension and the distal suture ends tensioned, the distal graft ends are fixed using an interference screw squeezed into the tibial tunnel as well as a cortical button with an adjustable loop setting through a transtibial ridge tunnel. Finally, the sartorius aponeurosis is repaired and the incisions and approaches are closed.

### **6.4 Rehabilitation Programs**

Participants included in this study will receive postoperative rehabilitation education orally, in written forms, and through WeChat online videos following the institutional SOP:

#### ① At 1–6 weeks (goals: swelling reduction; normal walking; knee flexion $>90^\circ$ )

Patients are allowed to bear weight with an ACL brace locking at full extension as tolerated immediately after the operation. Patients should abandon the walking stick and brace by 2 and 4 weeks, respectively. Muscle strength exercises include ankle pumps, isometric contraction of quadriceps, straight leg raises, and calf raises. Range of motion exercises include patellar mobilizations, heel slides, seated assisted flexion, and leg pressing.

#### ② At 7–12 weeks (goals: flexion $>120^\circ$ ; extensor strength and proprioception training)

Patients should continue carrying out flexion and extension exercises (active assisted  $\rightarrow$  active). Muscle strength exercises include squatting ( $0\text{--}45^\circ$ ) and resistive knee extension ( $0\text{--}5\text{ kg}$ ). Flexibility exercises include step-ups/downs and stationary bikes.

#### ③ At 4–6 months (goals: flexor strength and balance training; running/non-pivoting sports)

Patients should aim at full knee flexion (if not reached yet) and extension (rather than hyperextension). Training programs include step-ups/downs, resistive knee flexion ( $0\text{--}10\text{ kg}$ ), squatting (double-leg  $\rightarrow$  single-leg), single-leg hops, and steady running.

#### ④ At 7–12 months (goals: strength and agility training; noncontact pivoting sports)

Training programs include single-leg hops for distance, side slides, shuttle sprints, side crossing steps, and specific training for targeted sports. Patients are encouraged to return to pivoting sports by 9 months, depending on radiological findings and sports readiness.

## **Section 7. Group Allocation**

### **7.1 Randomization**

Prior to the beginning of participant enrollment, a random number sequence with 120 numbers (with 60 odd numbers for allocation to the intervention group and 60 even numbers for allocation to the control group) will be generated by computer. Then, the 120 sheets (each printed with one random number as generated) will be separately and sequentially sealed in 120 numbered opaque envelopes. The number sequence for group allocation will not be predictable. An independent trial assistant will be responsible for generating random numbers and keeping the envelopes. This assistant should be blocked contact with participants and investigators who should be concealed to the group allocation in this study.

For each participant, the randomization should be performed after surgery; otherwise, the postoperative exclusion may cause imbalanced allocation, and the risk of allocation leakage to surgeons may increase. Once the participant is rechecked for inclusion and exclusion criteria and given the enrollment and randomization numbers (corresponding to the envelopes), the group allocation (intention-to-treat) will not be changed.

### **7.2 Allocation Concealment**

In a preliminary survey about motivation to participate, we introduced 2 patterns of allocation concealment to patients with ACLR: (1) double-blinded: all participants receive blood withdrawal, while only participants in the intervention group would receive real PRP injection; (2) single-blinded: participants in both groups are aware of group allocation, and only participants in the intervention group would receive the blood withdrawal and PRP injection. The results showed that 9 in 10 vs 2 in 10 respondents were willing to participate in the single- and double-blinded trials, respectively. Compared to traditional double-blinded designs with placebo control, the control group in PRP studies would receive additional blood withdrawal without any potential therapeutic benefits. Given the motivation for participation and potential ethical concerns, participants will be aware of their own group allocation.

The investigators who have the accessibility to treatment, outcome measurements, and data curation should be blinded throughout the study, including the surgeons, physical therapists, clinicians for informed consent, data entry, physical examinations, and radiological measurements, as well as the statistician. Participants will be instructed not to disclose their group allocation to these investigators before each follow-up visit. For each participant, the participant contacting assistant will be responsible for coordinating follow-up visits, taking the opaque envelope from the independent randomization assistant, and revealing the group allocation to the participant at the first follow-up visit. This assistant should be inaccessible to the treatment, outcome measurements, and data curation processes.

## **Section 8. Intervention and Control**

### **8.1 Intervention**

Participants allocated to the intervention group will receive blood withdrawal followed by PRP injection at 4 weeks ( $\pm 3$  days), 8 weeks ( $\pm 5$  days), and 3 months ( $\pm 7$  days) during the routine follow-up visits (after clinical assessments) following the standardized protocol:

#### **① Materials for treatment**

PRP preparation kit (containing a 50-mL syringe, three 20-mL syringes, 2 centrifuge tubes, 2 pipettes, 5 mL of Anticoagulant Citrate Dextrose Solution A, and several puncture needles), centrifuge (maximum speed, 4000 r/min; maximum force, 2826 g), automated hematology analyzer, and conventional injection equipment.

#### **② Whole blood withdrawal**

After skin sterilization, 45 mL of venous blood is drawn from the antecubital fossa into a 50-mL syringe with 5 mL of anticoagulant preloaded in the syringe.

#### **③ PRP preparation**

The 50 mL of whole blood is transferred into a centrifuge tube and centrifuged at 260 g for 10 minutes. After centrifugation, the sample is separated into 3 layers (from bottom to top: red blood cells, buffy coat containing, and acellular plasma). The upper and middle layers are aspirated into a new centrifuge tube using a pipette. The sample is recentrifuged at 360 g for 15 minutes and separated into 2 layers. Then, a new pipette is used to aspirate the supernatant (platelet-poor plasma) and leave 5 mL of leukocyte-poor PRP in the tube. Blood cell counts of whole blood and PRP are analyzed using an automated hematology analyzer.

#### ④ Intra-articular injection

The PRP should be injected into the knee within 45 minutes after blood withdrawal. With the patient in the sitting position and the knee flexed at 90°, the injection needle is punctured through the knee anterolateral approach (lateral to the patellar tendon and superior to the joint line) towards the intercondylar notch under ultrasound guidance. After injection, passive knee flexion and extension are implemented for 10 cycles. Patients are instructed to rest for 30 minutes in the treatment room for observation of adverse events.

## 8.2 Control

Participants allocated to the control group will undergo the same timing and assessments of follow-up visits without postoperative knee injection. Participants in both groups should avoid co-interventions which may cause confounding biases, including unscheduled knee injection and non-steroidal anti-inflammatory drugs, while acetaminophen can be prescribed for participants who report a moderate to severe pain if required (should be suspended for 7 days before clinical assessments). If participants receive additional medications or treatment out of the protocol, they should report them completely to the clinicians at follow-up visits.

## Section 9. Follow-up Visits

|                          | Pre-op | Post-op | 4 wk | 8 wk | 3 mo | 6 mo | 12 mo |
|--------------------------|--------|---------|------|------|------|------|-------|
| Participant recruitment  |        |         |      |      |      |      |       |
| Eligibility screening    | √      |         |      |      |      |      |       |
| Informed consent         | √      |         |      |      |      |      |       |
| Data collection          | √      |         |      |      |      |      |       |
| Rehabilitation education |        | √       |      |      |      |      |       |
| Randomization            |        | √       |      |      |      |      |       |
| PRP injection by group   |        |         |      |      |      |      |       |
| Intervention group       | ×      | ×       | √    | √    | √    | ×    | ×     |
| Control group            | ×      | ×       | ×    | ×    | ×    | ×    | ×     |
| Outcome measures         |        |         |      |      |      |      |       |
| Primary outcome          | √      |         |      |      |      |      | √     |
| Subjective assessments   | √      |         |      |      | √    | √    | √     |
| Radiological scanning    | √      |         |      |      | √    | √    | √     |
| Physical examinations    | √      |         | √    | √    | √    | √    | √     |
| Adverse events           | √      |         | √    | √    | √    | √    | √     |

## Section 10. Outcome Measures

### 10.1 Primary Outcome

The primary outcome of this study is the KOOS4 score at 12 months postoperatively. The KOOS has been developed for evaluating knee symptoms and function in a variety of knee injuries and osteoarthritis and validated in ACL-injured and ACL-reconstructed patients. KOOS includes 42 items covering 5 subscales: pain (9 items), symptoms (7 items), function in activities of daily living (17 items), function in sports and recreation (5 items), and quality of life (4 items). For each item, the responses are presented in 5-point Likert scales (range, 0–4). For each subscale, the overall scores are summed by each item and standardized to range from 0 to 100, with higher scores indicating fewer symptoms or better knee function (100 indicating best knee function without symptoms). Given that patients with ACL injuries and ACLR have relatively high scores of the function in activities of daily living subscale, some high-level studies have introduced KOOS4, which is calculated as the average score of the other 4 subscales (pain, symptoms, function in sports and recreation, and quality of life), to avoid the ceiling effect. Based on the anchor-based MCIDs for each subscale of the KOOS, the MCID for KOOS4 is determined as 13 points in this study.

### 10.2 Secondary Outcomes: Subjective Assessments

#### ① Global Rating of Change (GROC) scale, at 12 months

GROC scale assesses the overall change of condition resulting from the treatment (including the surgery and postoperative treatment). Scores range from –7 (a very great deal worse) to +7 (a very great deal better), with higher positive values indicating more improvement, and scores  $\geq +3$  (somewhat better) are considered as clinically meaningful.

#### ② KOOS subscales, at 3, 6, and 12 months

The MCIDs for KOOS subscales of pain, symptoms, activities of daily living, sports and recreation, and quality of life are 16.7, 10.7, 18.4, 12.5, and 15.6, respectively.

#### ③ P4 score for pain, at 3, 6, and 12 months

The visual analog scale (VAS) for pain is assessed on a straight horizontal line; scores range from 0 (no pain) to 10 (worst pain possible), with 1–3 indicating mild pain, 4–6 indicating moderate pain, and 7–10 indicating severe pain. To comprehensively evaluate the pain in different timing and conditions, the P4 score is calculated as the sum of VAS scores at 4 timepoints (morning, afternoon, evening, and with activity) during the past 2 days.

④ Tegner score, at 3, 6, and 12 months

Tegner Activity Scale assesses the highest level of current sports participation. Scores range from 0 (sick leave or disability) to 10 (professional level of competitive sports), with higher values indicating higher levels of sports activities, and scores  $\geq 6$  are considered as return to pivoting sports. The MCID (as minimally detectable) for Tegner score is 1.

⑤ Lysholm score, at 3, 6, and 12 months

Lysholm Knee Questionnaire is specifically designed for ligament injuries and includes 8 items regarding subjective perceptions (such as instability, pain, and locking). Scores range from 0 to 100, with higher values indicating fewer symptoms and better knee function in daily living. The MCID for Lysholm score is 10.7 (distribution-based, from our data).

⑥ Subjective IKDC score, at 3, 6, and 12 months

IKDC Subjective Knee Form includes 18 items covering 3 domains (symptoms, sports activities, and function). Scores range from 0 to 100, with higher values indicating better knee conditions. The MCID for IKDC score is 10.4 (distribution-based, from our data).

### 10.3 Secondary Outcomes: Radiological Evaluation

Participants included in this study will undergo magnetic resonance imaging (MRI) scanning at 3, 6, and 12 months. A 3.0-T MRI unit (MAGNETOM Prisma, Siemens) is selected for standardization of the radiological evaluation. The institutional protocol of conventional sequences for knee MRI include axial, sagittal, and coronal planes of T1-weighted imaging and fat-saturated proton-density-weighted imaging (FS-PDWI), with a slice thickness of 3 mm. In particular, the sagittal plane is determined by the vertical plane of the line tangent to the posterior cortices of medial and lateral femoral condyles on the axial plane.

The graft maturity will be evaluated on sagittal FS-PDWI sequences (repetition time, 3010 ms; echo time, 44 ms) using 0.1-cm^2 circular regions of interest (ROIs) for measuring the signal intensity. For the signals of background and quadriceps tendon, the ROIs are placed at 2 cm anterior to the patellar tendon and patellar upper limit level, respectively. For the signals of ACL graft, the anteromedial and posterolateral bundles are both separated into 3 sections: (1) femoral intra-tunnel graft, (2) intra-articular graft, and (3) tibial intra-tunnel graft. In each section, 3 ROIs are selected to calculate the mean signal. Signal-to-noise quotients (SNQ) are separately calculated for the 6 sections of the ACL graft using the following formula:

$$\text{SNQ} = \frac{\text{Signal of ACL Graft} - \text{Signal of Quadriceps Tendon}}{\text{Signal of Background}}$$

All measurements will be performed on RadiAnt DICOM Viewer by 2 independent investigators who are blinded to group allocation. The interrater reliability will be evaluated using the intraclass correlation coefficient (ICC), with ICCs  $\geq 0.75$  indicating good reliability. The signal intensity on FS-PDWI usually reflects water content and vascularity, with lower SNQ values indicating a latter period of graft remodeling and better graft maturity.

#### **10.4 Secondary Outcomes: Physical Examinations**

① Knee range of motion, at each follow-up

The active-assisted range of motion is measured by placing the axis of a goniometer over the lateral femoral epicondyle and lining the two arms along the femoral and fibular axes, with positive values indicating knee flexion and negative values indicating hyperextension. The knee flexion and extension are assisted by both arms of the participant (in the sitting position) and a firm pillow beneath the heel (in the supine position), respectively.

② Knee circumference, at each follow-up

The knee circumference is measured by placing a tape measure circumferentially around the knee at the mid-patellar level while the participant is in the supine position with full knee extension. Results are presented as the side-to-side differences by subtracting the circumference of the contralateral knee, with higher positive values indicating worse swelling.

③ Knee laxity, at 12 months

The anterior drawer and Lachman tests are used to assess knee anteroposterior laxity at 90° and 30° of flexion by manual, respectively; grades include 0 (0–2 mm), 1 (3–5 mm), 2 (6–10 mm), and 3 (>10 mm). The pivot-shift test is used to assess knee rotatory laxity by manual; grades include 0 (negative), 1 (glide), 2 (clunk), and 3 (gross reduction). A KT-1000 arthrometer is used for quantitative measurements of anterior tibial translation at 30° of knee flexion, with higher results indicating increased knee anteroposterior laxity.

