Platelet-rich plasma (PRP) is a biological product made from autologous blood through centrifugation and degranulation steps, with good records of safety and promising efficacy in therapy for musculoskeletal disorders. The platelet concentration of PRP is about 3–5 times that of whole blood, with enrichment of growth factors and cytokines; hence, PRP is widely recognized to have a potential for promotion of healing after tissue injury or repair, which has attracted the interest of researchers in orthopedics and sports medicine. Cell and animal studies have shown that PRP can promote skeletal muscle regeneration, reduce cell apoptosis, regulate tissue differentiation, and inhibit adhesion and fibrosis. When it comes to clinical application, the actual effect of PRP is controversial. Systematic reviews have demonstrated that PRP injection resulted in clinical improvements in patients with lateral epicondylitis and knee osteoarthritis, with regard to ACLR, the application of PRP-pretreated grafts was ineffective in promoting graft-to-bone healing and preventing tunnel widening, while intraoperative injection of PRP in the graft harvesting area and bone tunnels may help reduce donor site pain and promote graft revascularization, respectively. It can be seen that the actual effect of PRP depends on the timing, locations, and methods of administration. Based

on the promising biological effects and good safety records of PRP in basic scientific research and clinical practice, we hypothesize that injecting the PRP into the joint cavity at fixed intervals after ACLR may result in reduction in knee symptoms related to edema and adhesion reactions as well as promotion of graft revascularization.

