## **Section 2. Purposes**

The main purpose of this study is to evaluate the clinical efficacy of postoperative intra-articular PRP injection on subjective outcomes (overall perception of pain, symptoms, function in sports activities, and quality of life) in patients with ACLR.

The secondary purposes of this study are to evaluate the various clinical and radiological outcomes (including pain, swelling, adhesion, and graft revascularization and maturation) during the first year after ACLR with or without postoperative intra-articular PRP injection.

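### Knee motion is compared as a raw, unreferenced angle: the randomised comparison stays unbiased, but it loses precision and the values cannot be read as motion lost to adhesion

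*Protocol*

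**What the plan says.** Section 10.4 ① measures active-assisted extension and flexion of the knee by goniometer at each follow-up, "with positive values indicating knee flexion and negative values indicating hyperextension". It states no contralateral reference, no change from baseline, no definition of a deficit and no direction of benefit.

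The next item, 10.4 ②, treats swelling differently: "Results are presented as the side-to-side differences by subtracting the circumference of the contralateral knee". It also states which direction is worse.

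Section 12.1 ① gives baseline-adjusted ANCOVA to the subjective assessments. Range of motion is neither a subjective nor a radiological outcome, so it falls under 12.1 ③: an unadjusted t test if the Kolmogorov-Smirnov test supports normality, otherwise a Mann-Whitney-Wilcoxon test. Section 6.2 collects preoperative range of motion and the Beighton score, but 12.1 uses neither for this outcome.

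Motion matters here because adhesion belongs to the secondary purposes in Section 2, "including pain, swelling, adhesion, and graft revascularization and maturation", and to the hypothesis in Section 1, "reduction in knee symptoms related to edema and adhesion reactions". Section 1 also names limited motion as a consequence of edema and adhesions.

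**The concern.** People differ in how far a healthy knee extends and bends. A raw angle adds that natural limit to whatever adhesion has taken away. Suppose a knee stops at 0° while the other knee reaches −8°. It has lost 8°, yet it reads the same as a knee that never went past 0° and has lost nothing. Within an arm, one knee at +5° and one at −5° average to 0°.

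Two things are at stake. First, reported values and arm means would invite a reading as extension deficit that they cannot bear. Second, variation unrelated to treatment stays in the error term although the plan collects a value that could remove part of it, so a real effect on motion would be harder to detect.

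**Working it through.** **The plan's own figures.** The document gives no figure for range of motion. Its sample size concerns KOOS4 and is used here only for the number per arm. With a difference of 13, SD 20, two-sided 0.05 and power 0.9 (Section 5), the noncentral t calculation gives power 0.896 at 50 and 0.902 at 51 per arm, so 51 reproduces. Then 51/0.85 = 60 per arm.

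**Model.** Observed extension = natural limit + motion lost. All values below are assumptions.

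**Step 1: an arm's mean against the contrast.** Let 20% or 40% of people hyperextend by 3–10° (mean 6.5°), and let 20% or 30% lose extension (mean 5° among those who do).

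| Hyperextending | Mean natural limit | Mean signed score at mean loss 1.0° | Mean signed score at mean loss 1.5° | Contrast |
|---|---|---|---|---|
| 20% | −0.2 × 6.5 = −1.3° | −0.3° | +0.2° | 0.5° |
| 40% | −0.4 × 6.5 = −2.6° | −1.6° | −1.1° | 0.5° |

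The arm means suggest full or better extension although motion has been lost. The contrast between the two loss levels is exactly the true 0.5° in both rows.

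A simulation of 20,000 trials (51 per arm, mean loss 4° against 2°, mean natural limit −3°) agrees. The mean difference was 1.99–2.00° at every natural SD tried. With natural SD 2°, 3° and 5°, 4%, 9% and 18% of knees that had lost at least 5° still read 0° or below.

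**Step 2: the cost in precision.** Assume a true difference in mean loss of 2°, SD of loss 4°, natural SD s, and a reference reading that equals the natural limit plus error of SD τ. The error variances are:

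- raw angle: 16 + s²
- plain difference from the reference: 16 + τ²
- reference as covariate: 16 + s² − s⁴/(s² + τ²) = 16 + s²τ²/(s² + τ²)

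The last term is never larger than s² or τ², so apart from one degree of freedom the covariate analysis is at least as precise as either alternative.

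Power = Φ(2/(σ√(2/51)) − 1.96), where √(2/51) = 0.198. For s = 3 on the raw angle, σ = 5, 2/0.990 = 2.020 and Φ(0.060) = 0.524. For the plain difference with τ = 1, σ = √17 = 4.123, 2/0.8165 = 2.449 and Φ(0.489) = 0.688.

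| s | Raw: variance, power | Difference, τ = 1 | Covariate, τ = 1 | Difference, τ = 2 | Covariate, τ = 2 |
|---|---|---|---|---|---|
| 0° | 16, 0.71 | 17, 0.69 | 16.0, 0.71 | 20, 0.62 | 16.0, 0.71 |
| 2° | 20, 0.62 | 17, 0.69 | 16.8, 0.69 | 20, 0.62 | 18.0, 0.66 |
| 3° | 25, 0.52 | 17, 0.69 | 16.9, 0.69 | 20, 0.62 | 18.8, 0.65 |
| 5° | 41, 0.35 | 17, 0.69 | 17.0, 0.69 | 20, 0.62 | 19.4, 0.63 |

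For 90% power the raw angle would need 106, 132 and 216 per arm at s = 2°, 3° and 5°, against 90 for the plain difference with τ = 1. At s = 0 the plain difference is worse than the raw angle, and more so as τ grows. The covariate analysis is not.

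**The case against.** The strongest reply is that the comparison is valid as planned. Each degree lost moves the score by one degree, whatever the natural limit, and randomisation balances that limit in expectation. A reader might infer that hyperextending knees cancel deficits in the group comparison. Step 1 shows that they do not: the offset happens inside an arm's mean and leaves the contrast untouched. A reader might also fear that a chance imbalance in hypermobile patients could pass for an effect. Its standard error is s√(2/51), or 0.40° to 0.99° for s from 2° to 5°, and the test's standard error already allows for it. The recorded Beighton score would also make such an imbalance visible.

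Nor do the documents support saying that the measure fails to capture adhesion. Flexion is measured at the same visits, Section 11.1 lists decreased range of motion and arthrofibrosis among the adverse events, and 4.3 identifies reoperation for lysis of adhesion. The adverse events have no threshold in degrees, so they add to the outcome without replacing it.

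It might further be inferred that a rank test scores hyperextension as better than neutral. Section 10.4 ① states no direction of benefit and testing is two-sided. The aim in 6.4 ③ of extension without hyperextension is a rehabilitation goal, not a scoring rule. The sign convention itself is ordinary goniometer notation and not an error.

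Finally, the size of the loss rests on assumed SDs, and with little natural variation there is none. All of this stands. It leaves a missing reference value that costs some precision and makes the reported angles hard to interpret.

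**Conclusion.** The point holds as one of precision and interpretation, and it is minor. The between-group comparison of range of motion is unbiased and its error rate is sound. What the plan gives up is an unknown amount of power on a secondary outcome, together with the ability to read an individual 0° or an arm's mean as motion kept or lost.

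Under the assumptions shown, power on the raw angle is 0.62 to 0.35 for natural SDs of 2° to 5°. With the reference as covariate it is about 0.69 if the reference error is 1°, and 0.66 to 0.63 if it is 2°. With no natural variation the loss is nil. The gain from the preoperative angle depends on how well it reflects the natural limit. The entry criterion of nearly normal motion in 4.1 helps, but a residual preoperative deficit would count as reference error. The calculation covers extension. The same reasoning applies to flexion, for which no figures were run. The primary outcome and the sample size are not affected.

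**What to change.** In 12.1, move knee extension and flexion from the unadjusted tests to ANCOVA with the preoperative angle of the same motion (6.2) as covariate, as 12.1 ① already does for the subjective scores. This needs no new data and costs one sentence and one degree of freedom.

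In 10.4 ①, also report extension and flexion deficit as side-to-side differences, both signed so that a positive value means lost motion: operated minus contralateral for extension, contralateral minus operated for flexion. The contralateral knee is a reasonable reference, because 4.2 excludes bilateral ACL injury, contralateral dysfunction and previous surgery on either knee, and it is already examined at each follow-up for circumference. The cost is one extra goniometer reading with its measurement error.

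The side-to-side difference should serve description and should not by itself replace the raw angle in the test. Plain differencing can lose power when natural variation is small (0.71 down to 0.62 at s = 0, τ = 2). If the contralateral angle is used in the test, it should enter as a covariate.
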